Anecdotally, psychological factors have long been believed to be associated with the development of frozen shoulder. Codman proposed a link between one’s constitution and the development of “frozen shoulder” when he first coined the term in 1934 and Coventry used the term “periarthritic personality” to describe these personal characteristics who “were a little run-down without anything particular the mater” [2, 29]. A number of authors have since looked at both personality traits and the mental health of patients with primary frozen shoulder [21, 25, 30–34]. The findings from these studies are conflicted and inconclusive and rely upon varying measures of personality and depression, although recent studies found that the mental health of patients with primary frozen shoulder was no different to that of the general population [32, 33]. No research has been done assessing a temporal relationship between depression and frozen shoulder’s related condition PSS. Given these historical views, depression’s known association with chronic pain and disability, and the described association of PSS with worker’s compensation claims we suggest that it is possible that patients who are depressed will be more likely to develop PSS [22, 26, 27].

The three aims of this study will be first to determine the incidence of postoperative stiff shoulder in patients of a single surgeon following arthroscopic subacromial decompression, and/or excision of the distal clavicle and/or rotator cuff repair rotator cuff repair; secondly, we will analyse the relationship between perioperative pain and depression, assessed by the Patient Health Questionnaire – 9, and the development of postoperative stiff shoulder, in patients following arthroscopic subacromial decompression, and/or excision of the distal clavicle and/or rotator cuff repair rotator cuff repair; thirdly, we will compare and contrast the incidences of postoperative stiff shoulder determined by different objective clinical criteria in the same patient cohort.

We hypothesize that patients who exhibit higher pain levels in the first month postoperatively will be more likely to develop PSS due to a more active postoperative inflammatory process. Secondly, we hypothesize that patients with depressed mood will be more likely to develop postoperative stiff shoulder. Thirdly, we hypothesize that different objective clinical criteria will determine different rates of postoperative stiff shoulder in the same patient cohort.

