### Sample size

Using the PASS^13^ software a two sample *T*-test assuming equal variance in both groups was performed. The power was set at 0.80 and the significance level (α) at 0.05. A clinically meaningful difference between the postoperative stiff shoulder and non-postoperative stiff shoulder groups was defined as a mean difference of 2 pain units [37, 38] on a scale of 0–10 and the standard deviation of these means was estimated from a previous randomised controlled trial of postoperative shoulder pain to be 2.20 [39]. Assuming a low incidence of postoperative stiff shoulder of 10 % a sample size of 110 patients was determined. To allow for loss to follow up and postoperative exclusion a 20 % margin was included resulting in a required sample size of 132 participants.

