### Analysis

The incidence of postoperative stiff shoulder will be determined using the treating surgeon’s clinical diagnosis informed by the Buchbinder criteria of restriction of motion of greater 30° in two or more planes of shoulder motion [40].

Patient demographics, baseline range of motion, pain, sleep and depression scores and outcome data will be presented for both outcome groups (postoperative stiff shoulder and no postoperative stiff shoulder).

The principal analysis will involve assessing whether or not a relationship exists between average pain scores and development of postoperative stiff shoulder. This will be by determining if there is a significant difference of the mean of the “average pain scores over the last 24 h” between both outcome groups at each recorded time point and over predetermined periods (first week postoperatively, first month postoperatively and from week four to ten postoperatively), adjusted for multiple comparisons using the Holm’s step down procedure [41].

Secondary analysis will assess depression and its relationship with PSS. A history of depression diagnosis as well as active depression at each time point, as assessed by the PHQ-9, will be assessed for an association with a diagnosis of PSS adjusted and not adjusted for baseline depression, and adjusted for multiple comparisons using the Holm’s step down procedure [41].

This study will also report the incidences of postoperative stiff shoulder after rotator cuff repair as well as subacromial decompression and excision of the distal clavicle not in association with rotator cuff repair.

Finally a series of range of motion criteria will be used to objectively determine a range of incidences of PSS in the same cohort (Table 1).

**Table 1 Tab1:** Criteria for diagnosing postoperative stiff shoulder

Criteria for diagnosing postoperative stiff shoulder
Clinician’s diagnosis
Range of motion thresholds in two planes, both required • Active elevation <100 degrees AND • Passive external rotation <30 degrees
Range of motion thresholds in two planes, at least one required • Active elevation <100 degrees OR • Passive external rotation <30 degrees
Restricted range of motion compared to contralateral side, at least two planes • Restriction of >30 degrees in TWO or more planes of movement
Restricted range of motion compared to contralateral side, at least three planes • Restriction of >30 degrees in THREE or more planes of movement

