## Discussion

The aims of the study will be to provide greater insight into the incidence of PSS post rotator cuff repair and report incidences of PSS post subacromial decompression and/or excision of the distal clavicle not in association with rotator cuff repair. A further aim is to identify whether increased pain levels can be used as a marker of patients who may benefit from early intervention to prevent or manage PSS. and to assess whether depression is a risk factor for the development of PSS. Finally we aim to compare and contrast the incidences of PSS determined by different objective clinical criteria in the same patient cohort.

The results of this trial we anticipate will contribute to our clinical understanding of the development of the postoperative stiff shoulder therefore improving clinical care and peri-operative information for patients. In addition it will provide a platform for discussion of how to objectively define this condition with the aim of assisting the development of a consensus definition.

Strengths of our prospective study will include the involvement of a single surgeon with set surgical protocols, statistical power to detect a clinically meaningful difference in pain scores, and the ability to assess a temporal relationship between pain, depression and postoperative stiff shoulder through the use of a cohort study. In addition the study will have the ability to determine the incidence rate of PSS after rotator cuff repair as well as in patients having a subacromial decompression without rotator cuff repair and also those undergoing an excision of the distal clavicle not in association with rotator cuff repair. These figures are absent from the current literature.

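### The 80% power is for one unadjusted t-test, but the principal analysis is 9 or 10 Holm-adjusted pain comparisons with none named as primary, and no single time point keeps 80%

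*Protocol article*

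**What the plan says.** **Sample size section.** The calculation is for one test: "a two sample *T*-test assuming equal variance in both groups was performed". "The power was set at 0.80 and the significance level (α) at 0.05". The target difference "was defined as a mean difference of 2 pain units", and the SD was "estimated from a previous randomised controlled trial of postoperative shoulder pain to be 2.20". "Assuming a low incidence of postoperative stiff shoulder of 10 % a sample size of 110 patients was determined". A 20% margin takes 110 to 132. Multiplicity is not mentioned.

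**Analysis section.** The principal analysis compares the mean 24-hour average pain score between patients with and without postoperative stiff shoulder (PSS). It does so at every recorded time point and "over predetermined periods (first week postoperatively, first month postoperatively and from week four to ten postoperatively), adjusted for multiple comparisons" with Holm's step-down method. No comparison is singled out as primary.

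**Outcome assessment section.** Pain is recorded preoperatively and at six postoperative phone calls: days 2, 5 and 7, and weeks 4, 7 and 10.

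**Background section.** The pain hypothesis is specific: "patients who exhibit higher pain levels in the first month postoperatively will be more likely to develop PSS".

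**Discussion section.** The listed strengths include "statistical power to detect a clinically meaningful difference in pain scores".

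**The concern.** The α in the sample-size calculation is not the α that the principal comparisons will face. Six calls plus three periods give nine tests, and the preoperative score would make ten. Under Holm the smallest p-value must be at or below 0.05/9 = 0.0056 (or 0.05/10 = 0.005) before anything can be declared. The one contrast that the hypothesis names, first-month pain, shares its error rate with weeks 7 and 10 and the week 4 to 10 period, which lie outside that hypothesis.

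At stake is how a null result is read. With about 11 expected PSS cases, a non-significant adjusted comparison could be taken as evidence against the pain hypothesis because the article says the study was powered for it.

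**Working it through.** **Inputs from the protocol.** Difference 2; SD 2.20; incidence 10%, so 11 PSS v 99 non-PSS among 110 evaluable; α = 0.05; six postoperative calls; three periods.

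**Assumptions not in the protocol.** Two-sided tests; SD 2.20 at every call; equal correlation ρ between calls, taken as 0.3, 0.5 and 0.7; period means as simple means of the calls they contain; all comparisons in one Holm family.

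**1. Reproduce the stated figure.** Noncentrality = 2 / [2.20 × √(1/11 + 1/99)] = 2 / (2.20 × 0.3178) = 2.860, with 108 degrees of freedom. At α = 0.05 the critical value is 1.982 and noncentral-t power is 0.809. With 10 v 90 it is 0.771. So 110 is the first multiple of ten to reach 80%, and the protocol's figure reproduces as a single unadjusted test.

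**2. Holm's first step, same noncentrality.**

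| Threshold | Critical t | Power | Difference detectable with 80% power |
|---|---|---|---|
| 0.05 | 1.982 | 0.809 | 1.98 |
| 0.05/9 | 2.830 | 0.515 | 2.57 |
| 0.05/10 | 2.866 | 0.500 | 2.60 |

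If all 132 were retained (13 v 119), first-step power would be 0.615 for nine comparisons and 0.602 for ten.

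**3. Full Holm.** Simulated with nine comparisons, 11 v 99, 6,000 to 10,000 runs per setting. Ranges are over ρ = 0.3 to 0.7, with simulation error of about 0.01.

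| True 2-point difference at | Each affected time point | First-month mean | At least one rejection |
|---|---|---|---|
| Week 4 only | 0.50–0.52 | 0.03–0.05 | 0.51–0.54 |
| The four first-month calls | 0.57–0.60 | 0.68–0.91 | 0.76–0.94 |
| All six calls | 0.64–0.68 | 0.70–0.92 | 0.80–0.97 |

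In the first row the first-month mean carries only a quarter of the difference (2/4 = 0.5 point). Adding the preoperative score, with no difference there, lowers the per-time-point figures to about 0.55–0.58 (first-month calls) and 0.60–0.64 (all six). No time-point comparison reaches 80% in any setting.

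**4. First-month mean as a single test at 0.05.** SD of a simple four-call mean = 2.20 × √[(1 + 3ρ)/4].

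| ρ | SD of mean | Power at 0.05 |
|---|---|---|
| 0.3 | 1.52 | 0.984 |
| 0.5 | 1.74 | 0.948 |
| 0.7 | 1.94 | 0.896 |

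Inside the Holm family, with the difference confined to the first month, the same contrast has about 0.91, 0.80 and 0.68.

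**The case against.** A reader might infer that the study simply has about 50% power. The documents do not support that. Fifty per cent is the first-step figure and applies when a single comparison differs. The hypothesis expects higher pain through the first month, so several comparisons should differ together and Holm's threshold relaxes as hypotheses are rejected. The Analysis section also asks whether a relationship exists at all. Power for at least one rejection is then relevant, and it exceeds 80% at low to moderate correlation. The first-month mean itself stays near or above 80% unless correlation is high. For the same reason, the enlarged sample that 80% power at the first step would require (about 180 evaluable for nine comparisons) is not a requirement for this study.

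It would also be wrong to call the analysis invalid, since Holm controls the family-wise error rate. Nor is testing later pain illegitimate: the second aim covers perioperative pain generally, and the Discussion wants pain as a marker for early intervention. The strength claim names neither 80% nor a time point, so it needs qualifying rather than deleting.

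One could add that an unseen analysis plan may rank the comparisons. However, the article itself fixes the sample-size α, the set of principal comparisons and the adjustment, and these do not match. Splitting time points and periods into separate Holm families would not rescue the time points either: first-step power at 0.05/6 is 0.570.

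What stands is that the stated power belongs to a test the plan does not single out, and every time-point comparison falls below it.

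**Conclusion.** The mismatch is real and moderate in size. The 80% (0.81 recomputed) is unadjusted. Under the planned Holm family of nine, power for a 2-point difference at a given time point is about 0.50 to 0.52 if it alone differs and about 0.57 to 0.68 if several differ. For the hypothesised first-month mean it is about 0.68 to 0.91, falling below 80% as correlation rises towards 0.7.

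The first-step figures rest on the protocol's own inputs plus a two-sided test. The full-Holm figures also rest on the assumed correlation, a constant SD, simple period means and a single family. The consequence is lost power and an overstated power claim, not bias or inflated error.

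**What to change.** Before outcomes are seen, name one primary comparison: PSS v no PSS on the first-month mean of the 24-hour average pain score, at two-sided α = 0.05. State how that mean is computed. A simple mean of days 2, 5, 7 and week 4 puts three quarters of its weight in the first week; any other weighting changes the SD and needs its own power figure, because the 0.90 to 0.98 above is for the simple mean. Move the remaining time points and periods to a secondary Holm family, and say whether the preoperative score belongs to it.

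If all comparisons are to stay co-primary, say in the Sample size section that the 80% is unadjusted, give the adjusted range with its assumptions, and qualify the strength claim in the Discussion to match.

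The cost is wording in the Sample size and Analysis sections, and in the Discussion if the second route is taken. No extra patients or data are needed. The drawback of the first route is that individual time-point results become secondary.

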**Method:**

A prospective cohort study involving 132 consecutive participants. Preoperatively, participants undergoing arthroscopic subacromial decompression and/or excision of the distal clavicle and/or rotator cuff repair will complete questionnaires about their levels of shoulder pain using a numerical rating scale from 0 to 10, and answer a Patient Health Questionnaire – 9 depression questionnaire. Postoperatively, the participants’ pain levels will be self-assessed at two, five and seven days and weeks four, seven and ten. They will complete the depression questionnaire twice, at the time of their routine first and final postoperative appointments with the treating surgeon. At the final appointment, approximately three months postoperatively, the treating surgeon will clinically diagnose participants as having a postoperative stiff shoulder or not. Their shoulders’ range of motion will be measured. The incidence of postoperative stiff shoulder will be determined, both pain and depression will be analysed as predictors for its development and incidences determined by different objective criteria will be compared.

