In our review of the literature surrounding frozen shoulder and PSS we found an array of criteria for both frozen shoulder and PSS. Objective criteria consisted of range of motion thresholds [5, 8, 10, 11, 13, 15, 18, 19, 27], global range of motion deficits compared to normal values [16], and range of motion deficits compared to the contralateral side [6–9, 11, 12, 14, 15, 17, 19]. We believe that the pursuit of a consensus objective criteria for PSS, and frozen shoulder, is important and we aim to apply various criteria to our patient cohort to determine their sensitivity and specificity of each test for the treating surgeon’s clinical diagnosis. We hope that these results will stimulate discussion on this issue.

We also reviewed the literature for studies researching the risk factors of PSS post rotator cuff surgery and found a number of studies, whose results conflicted [5, 10, 13, 22, 26, 28]. There is a scarcity of literature analysing the incidence of PSS after subacromial decompression or excision of the distal clavicle not in association with rotator cuff repair.

There are a number of potential risk factors for frozen shoulder and PSS that have been studied. These include sociodemographic, medical and psychological factors. Age, a traditional risk factor for primary frozen shoulder has been found to be and not be associated the development of PSS, with both higher and lower age associated with PSS in separate studies [10, 13, 28]. Our review found multiple studies associating worker’s compensation claims with the development of PSS, however one study rebutted these findings [22, 26, 28].

Diabetes, another traditional risk factor for primary frozen shoulder, has been found to be and not be associated with the development of PSS [10, 22]. Multiple studies have shown that patients with PSS after rotator cuff surgery have higher pain levels at 12 weeks with one study also finding that higher pain levels at six weeks were associated [10, 22, 28]. No studies have assessed the relationship between pain levels in the first month postoperatively, the time when the initial inflammatory healing process begins, and the development of PSS.

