Postoperatively participants will be clinically followed up at multiple time points. The operating surgeon will assess them at both their first and final postoperative consultations. The first consultation around the time of suture removal, and the second consultation three months after the operation. In addition the investigator will contact them by phone postoperatively on days two, five and seven and additionally at weeks four, seven and ten. At both postoperative surgeon clinical assessments the participants will asked to complete the PHQ-9. This will assess their mood over the previous two weeks. At their final postoperative consultation the range of motion of their treated shoulder will also be assessed. The senior surgeon will determine clinically whether or not the patient has ‘postoperative stiff shoulder’.

During each of the follow up phone calls, participants will be asked to complete the same pain questionnaires as preoperatively with the use of a verbal NRS and to detail the types of analgesia, dosage and any other treatment they have received in the last 24 h. The preoperative sleep assessment, using a verbal NRS, will be preformed postoperatively at these times. Participants will be asked what type and dosage of mediation (if any) they have taken to help them sleep in the last 24 h. Lastly patients will be asked to describe their mood over the past 24 h and also describe any events or stressors that may have impacted upon their pain, sleep or mood. This will be recorded on specifically designed form (see Additional file 3). Therefore each participant will have six phone assessments over the three months.

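### The three-month PHQ-9 is completed at the visit where postoperative stiff shoulder is diagnosed, so it is a concurrent correlate and should not be tested as a risk factor

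*Protocol article*

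**What the plan says.** All references are to the protocol article.

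- **When the outcome is recorded.** Abstract, Method: "At the final appointment, approximately three months postoperatively, the treating surgeon will clinically diagnose participants as having a postoperative stiff shoulder or not". Outcome assessment agrees, and describes no earlier postoperative assessment of stiffness or range of motion.
- **When depression is recorded.** There is a preoperative PHQ-9 and a baseline question on history of depression. After surgery, "At both postoperative surgeon clinical assessments the participants will asked to complete the PHQ-9". The Abstract confirms the timing: "They will complete the depression questionnaire twice, at the time of their routine first and final postoperative appointments with the treating surgeon". On the recall window, Outcome assessment says: "This will assess their mood over the previous two weeks".
- **How depression is analysed.** Analysis: "active depression at each time point, as assessed by the PHQ-9, will be assessed for an association with a diagnosis of PSS". This is done with and without adjustment for baseline depression, under one Holm procedure that also covers depression history.
- **How the results are to be read.** The Abstract says pain and depression will be analysed as predictors. The Discussion names depression as a possible risk factor and lists as a strength "the ability to assess a temporal relationship between pain, depression and postoperative stiff shoulder".
- **Pain.** The principal analysis compares mean pain at each recorded time point and over three periods (first week, first month, weeks 4 to 10). The Background hypothesis is narrower: "patients who exhibit higher pain levels in the first month postoperatively will be more likely to develop PSS".

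**The concern.** A risk factor has to be measured before the outcome it is meant to predict. The three-month PHQ-9 is not: exposure and outcome are recorded at the same visit, and the two-week recall covers a period in which a stiff, painful shoulder may already be present. If depressed mood is commoner in the PSS group at that visit, the data cannot say whether mood led to stiffness or stiffness to low mood.

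The plan gives this test the same standing as depression history and the earlier PHQ-9s, and its summary claims make no exception for it. A positive result at three months alone could therefore be reported as support for depression as a risk factor, or for early intervention, when it supports neither.

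Late pain raises a milder form of the same question. The Background notes earlier reports that "patients with PSS after rotator cuff surgery have higher pain levels at 12 weeks", and one study found the same at six weeks. That is what one would see if late pain were partly a symptom of stiffness already under way.

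**Working it through.** The article has no figure that depends on this point. The check sets the visit schedule against the analyses and claims.

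**Step 1. Gap between each exposure and the diagnosis.** Three months is taken as about week 13.

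| Exposure | When measured | Gap to diagnosis |
|---|---|---|
| Depression history | Baseline | about 13 weeks or more |
| PHQ-9, first | Preoperative | about 13 weeks or more |
| PHQ-9, second | First consultation, around suture removal | precedes the diagnosis visit |
| PHQ-9, third | Three-month consultation | 0 (recall about weeks 11 to 13) |
| Pain, days 2, 5, 7 | Phone | about 12 weeks or more |
| Pain, week 4 | Phone | 13 − 4 = 9 weeks |
| Pain, week 7 | Phone | 13 − 7 = 6 weeks |
| Pain, week 10 | Phone | 13 − 10 = 3 weeks |

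Only the third PHQ-9 coincides with the diagnosis. That is one of three PHQ-9 assessments, and one of four depression exposures when history is counted.

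**Step 2. Does baseline adjustment help?** It accounts for depression already present before surgery. Low mood that develops after surgery because the shoulder is stiff is not in the baseline value, so it remains in the adjusted association.

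**Step 3. What the change does to the depression family.** Assume one test per exposure and α = 0.05. The first Holm step is now 0.05/4 = 0.0125. Without the three-month PHQ-9 it is 0.05/3 = 0.0167. If the adjusted and unadjusted versions are counted separately, both thresholds are smaller. This is a side benefit and does not measure the temporal problem.

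**Step 4. Pain, for comparison.** The inputs from Sample size are a difference of 2, SD 2.20, α = 0.05 (taken as two-sided) and 10 % incidence in 110 patients, so 11 against 99. The noncentrality is 2 / (2.20 × √(1/99 + 1/11)) = 2.86 on 108 degrees of freedom. Power is 0.809, so the planned 110 reproduces. At the first Holm step:

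| Pain tests in the family | Threshold | Power |
|---|---|---|
| 9 (six postoperative points, three periods) | 0.05/9 = 0.0056 | 0.515 |
| 6 (without week 7, week 10, weeks 4 to 10) | 0.05/6 = 0.0083 | 0.570 |
| 10 (as 9, plus preoperative pain) | 0.05/10 = 0.0050 | 0.500 |
| 7 (as 6, plus preoperative pain) | 0.05/7 = 0.0071 | 0.549 |

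Dropping the late pain tests would gain about 5 percentage points on either count (0.570 − 0.515 = 0.055; 0.549 − 0.500 = 0.049). That is a multiplicity cost and says nothing about whether late pain is a precursor or a symptom.

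**The case against.** The strongest reply has three parts.

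1. **The Analysis section says association, not prediction.** Results are specific to each time point and share only a Holm correction, so a reader can see which visit produced a finding. This is correct, and the quoted sentence is not false in itself. It does not settle the matter, because the Abstract and Discussion supply the predictor, risk-factor and temporal wording without excluding the three-month PHQ-9.

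2. **Late pain is not cross-sectional.** A reader might infer that week 7, week 10 and weeks 4 to 10 fail in the same way and should leave the principal family. The documents do not support that. These scores come about 6 and 3 weeks before the recorded diagnosis and can forecast it statistically. The second aim concerns perioperative pain generally, and the Discussion seeks a marker for preventing or managing PSS, which need not be a cause. The first-month hypothesis already has its own prespecified period. Keeping or removing the late tests is a trade-off.

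3. **Nothing shows that the reverse direction is the likelier one.** This also stands. The article has no data on when stiffness begins, so one can say that direction is undetermined but not that an association more probably runs from stiffness to pain or mood.

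What remains of the late-pain question is a limit on interpretation. With no stiffness assessment between surgery and three months, late pain as precursor cannot be told from late pain as early symptom.

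**Conclusion.** The point holds for the three-month PHQ-9. Its association with PSS is cross-sectional by design, baseline adjustment does not change that, and the plan's claims about depression should not rest on it. It affects one of four depression exposures. The size of any bias cannot be calculated from the documents.

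The conclusion assumes that the Analysis wording on time points includes the final visit, as its plain reading does, and that PSS is diagnosed only at that visit, as the Abstract and Outcome assessment both state.

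A reader might go further and conclude that the cohort offers no temporal information at all. That would be wrong: depression history, the preoperative and first-consultation PHQ-9, and all the scheduled pain scores precede the recorded diagnosis. For pain the conclusion is only a caveat on how the week 7, week 10 and weeks 4 to 10 results are read.

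**What to change.** - In Analysis, limit the depression risk-factor tests, and their Holm family, to depression history and the preoperative and first-consultation PHQ-9.
- Report the three-month PHQ-9 separately, labelled as a concurrent correlate of PSS.
- In the Discussion, restrict the temporal-relationship claim to exposures measured before the diagnosis visit, and align the predictor wording in the Abstract.
- Keep the late pain comparisons if wanted, but state that they may reflect early symptoms or serve as markers, and that the Background hypothesis on pain will be judged on the first-month comparisons.

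The cost is a few sentences, with no new data, visits or patients. The downside is that the three-month depression result becomes descriptive.

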#### Outcome assessment

Baseline data collected from participant will include sex, age, dominant arm, shoulder side undergoing operation, history of diabetes mellitus and present treatment for diabetes mellitus, third party compensation status, history of depression, time since diagnosis of depression, whether participant is presently receiving treatment for depression and whether and type of previous surgery the participant has had on the shoulder undergoing operation (see Additional file 1).

Preoperatively participants will have range of motion assessed and be asked to complete a questionnaire encompassing pain, analgesia, sleep and mood (see Additional file 2). Range of motion of the shoulder will be assessed for each of the following planes of motion: active elevation, passive glenohumeral abduction with stabilisation of the scapula, passive external rotation in adduction and passive internal rotation in 90°, or maximal, abduction. This will be done using a goniometer. Average pain, worst pain at rest whilst seated with the arm at the side, worst pain with movement and worst pain at night over the last 24 h will be assessed using a visual numerical rating scale (NRS). The NRS pain scale is an 11 point scale where 0 = no pain and 10 = worst possible pain. Participants will be asked to detail the types of analgesia, dosage and treatment they have received in the last 24 h. Sleep will be assessed using a visual NRS sleep scale where 0 = worst possible sleep and 10 = best possible sleep. Participants will be asked what type and dosage of mediation (if any) they have taken to help them sleep in the last 24 h. Last, participants will be provided with a Patient Health Questionnaire – 9 (PHQ-9) that will assess their mood and depressive symptoms over the past two weeks and they will be classified as depressed or not depressed according to the DSM-IV criteria for a major depressive episode [35]. The PHQ-9 has a sensitivity of 98 % and specificity of 80 % for major depressive disorder when using the cutoff of 11 points or greater and allows for stratification of depression severity [35, 36].

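### The depression analysis names only baseline depression as a covariate; a sensitivity analysis adding compensation status, already recorded and cited in support of the hypothesis, should be prespecified

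*Protocol article*

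**What the plan says.** The Analysis section makes depression the subject of the secondary analysis. History of depression and PHQ-9 depression at each time point "will be assessed for an association with a diagnosis of PSS adjusted and not adjusted for baseline depression". The only other adjustment in that sentence is for multiplicity: "adjusted for multiple comparisons using the Holm’s step down procedure".

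The Background reviews risk factors and reports "multiple studies associating worker’s compensation claims with the development of PSS, however one study rebutted these findings". It then lists three grounds for the depression hypothesis: long-held opinion, the tie between depression and lasting pain or disability, and the compensation finding. The last is worded: "the described association of PSS with worker’s compensation claims we suggest that it is possible that patients who are depressed will be more likely".

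The Outcome assessment section records "third party compensation status, history of depression" among the baseline items. The Discussion states the aim of finding out whether depression is a risk factor for PSS.

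**The concern.** Using a compensation-PSS link to argue for a depression-PSS link makes sense only if compensation and depression tend to occur together. A baseline characteristic related to both exposure and outcome is a candidate confounder, and here the article's own reasoning puts it forward.

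The planned adjustment does not deal with it. Conditioning on baseline depression leaves open any route from compensation to postoperative depression and to PSS. It also does nothing for the comparison of baseline depression itself. The planned table of characteristics by outcome group is descriptive.

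What is at stake is attribution. If depression and PSS turn out to be associated, the analysis as described would not show how much of the association is shared with compensation status, while the Discussion wants to speak of a risk factor.

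**Working it through.** **1. The plan's own figure.** The Sample size section gives a difference of 2 units, SD 2.20, power 0.80, alpha 0.05 and 10% PSS. Taking the test as two-sided with a 1:9 split, the normal formula gives 11 + 99 = 110, as stated; the exact t test has power 0.809 there. The 132 is 110 × 1.20. So about 110 × 0.10 = 11 PSS cases are expected (13 if all 132 are evaluable). This calculation is for pain; the article gives none for depression.

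**2. Assumed inputs.** The article gives no compensation prevalence, no effect size for compensation and no depression prevalence by compensation status. I assumed:
- compensated share pc: 10%, 20%, 30%
- depression prevalence: d1 = 20% or 30% if compensated, d0 = 10% otherwise
- risk ratio RR of PSS for compensation: 2, 3, 4
- overall PSS: 10% (Sample size section)
- no effect of depression itself

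**3. Formulas.**
- p0 = 0.10 / (1 − pc + pc × RR); p1 = RR × p0
- P(dep) = pc × d1 + (1 − pc) × d0
- P(PSS | dep) = [pc × d1 × p1 + (1 − pc) × d0 × p0] / P(dep)
- P(PSS | not dep) = [pc × (1 − d1) × p1 + (1 − pc) × (1 − d0) × p0] / [1 − P(dep)]
- The crude odds ratio (OR) follows from these two risks.

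**4. Worked example: pc = 0.2, d1 = 0.3, d0 = 0.1, RR = 3.**
- p0 = 0.10 / 1.4 = 0.0714; p1 = 0.2143
- P(dep) = 0.06 + 0.08 = 0.14
- P(PSS | dep) = (0.06 × 0.2143 + 0.08 × 0.0714) / 0.14 = 0.1327
- P(PSS | not dep) = (0.14 × 0.2143 + 0.72 × 0.0714) / 0.86 = 0.0947
- OR = (0.1327 / 0.8673) / (0.0947 / 0.9053) = 1.46, where the truth is 1.00

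**5. Range.**

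| pc | RR | d1 v d0 | Crude OR |
|---|---|---|---|
| 0.1 | 2 | 20% v 10% | 1.09 |
| 0.2 | 3 | 30% v 10% | 1.46 |
| 0.2 | 4 | 30% v 10% | 1.62 (largest in the grid) |
| any | 1 | any | 1.00 |
| any | any | 10% v 10% | 1.00 |

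A wider grid (compensation-PSS odds ratio 2 to 5, d1 up to 40%) gives 1.08 to 1.90. The last two rows show that the bias vanishes if either link is absent.

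**6. Bias against sampling error.** In the example with N = 110, the expected counts are 2.0 depressed with PSS, 13.4 depressed without, 9.0 not depressed with PSS and 85.6 not depressed without.
- SE of log OR = √(1/2.04 + 1/13.36 + 1/8.96 + 1/85.64) = 0.83
- Bias = log(1.46) = 0.38, less than half of one standard error
- Approximate 95% interval around 1.46: 0.29 to 7.4

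**7. False positives.** I simulated two-sided Fisher tests for the example and counted only results in the harmful direction. At an unadjusted 0.05 the chance is about 6.7%, against 2.2% with no confounding. At Holm's first step with four depression contrasts (my count: history, preoperative and two postoperative PHQ-9 assessments; threshold 0.05 / 4 = 0.0125) it is about 2.0% against 0.5%, for any one contrast.

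**The case against.** The strongest reply is that this is a condensed article. Extra covariates for a secondary analysis are ordinary content for an analysis plan, and naming baseline depression need not mean that nothing else may be added. That stands as a reason for restraint: a plan that is not shown may already include compensation. It does not remove the point, because the article states a specific adjustment, and that adjustment leaves out a factor that its own rationale relies on.

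A reader might go further and infer that compensation is an established confounder, so that a positive depression result could not be interpreted. The article does not support that:
- It reports no association between compensation and depression, and it calls the compensation-PSS evidence conflicting: "compensation claims with the development of PSS, however one study rebutted these findings".
- Direction is open. Depression may precede a claim or help to explain why claimants develop PSS. Adjustment would then remove part of the effect being sought.
- The Abstract also asks whether depression can serve as a clinical predictor or a marker for early intervention. An unadjusted association answers that question.
- The size is assumed, is smaller than sampling error, and is further limited by Holm.

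It can also be said that age and diabetes have conflicting evidence in the Background and are recorded too. That is true, and about 11 cases will not support a long list. Compensation has the better claim to the single place because it alone of the three is used to argue for the depression hypothesis.

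**Conclusion.** The point holds in a limited form. As described, the depression analysis adjusts only for baseline depression, while a recorded baseline factor cited in support of the hypothesis is left out. If compensation is related to both depression and PSS, part of an observed association could be due to it. Under the assumed inputs the crude odds ratio is about 1.1 to 1.6 with no true effect, and 1.00 if either link is missing. This is possible bias, not demonstrated bias, and with about 11 PSS cases sampling error is the larger problem. What is affected is the step from an association to calling depression an independent risk factor; its use as a predictor or marker is not.

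**What to change.** In the Analysis section, prespecify a sensitivity analysis that adds third party compensation status as a single covariate to the depression-PSS model, by Firth-penalised logistic regression or Mantel-Haenszel stratification, and report it beside the planned estimate. State in advance that if the estimate shifts materially, depression will be described as a marker or predictor and not as an independent risk factor. Settle the wording before outcomes are seen.

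The cost is a change of text only, since the variable is already collected. One more term with about 11 cases widens the interval. If compensation lies downstream of depression, the adjusted estimate will be over-adjusted, so neither estimate should be shown without the other.
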